#### Voluntary withdrawal of participants

For whatever reason, the subjects are reluctant or unable to keep the clinical trial.Although subjects are not explicitly proposed to withdraw from the trial, they are no longer subject to treatment and examination and lost to follow-up.

#### Conditions for suspension

Any serious adverse event (SAE) takes place during the treatment period.Any gross fault is found in the clinical trial plan, which leads to difficulty in estimating treatment efficacy.Any significant deviation in the implementation of the protocol, if continues, it will be difficult to estimate treatment efficacy.The principal investigator requests to discontinue the trial.The drug supervision and administration department request to suspend the trial.

### Sample size calculation

According to our previous studies, on the basis of maintaining the original lipid-lowering therapy, in contrast with placebo, SMYA is expected to increase the plaque minimum fiber cap thickness (PMFCT) by an average of 40% µm. The standard deviation of the experimental group in the intervention of carotid plaque FCT is about 38, and the control group is about 36. This trial is designed as a 1:1 parallel control, α = 0.01, power = 90%, two-sided test, and the SAS (6.12) is adopted to evaluate the sample size. According to the calculation, 36 participants are needed for each group. After considering drop-out rates, the sample size of this protocol is 43 participants in the intervention group and the control group respectively, with a total of 86 cases.

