Yet, the previous atherosclerosis-related TCM research mainly focused on experiments and mechanism exploration, clinical studies were few. Meantime, in terms of efficacy indicators, most clinical studies were limited to assessing the effect of TCM on inflammatory factors and blood lipids in serum or using primary or subjective means such as ultrasound to evaluate As plaque. High-quality randomized, double-blind, and controlled studies on the treatment of As in TCM are lacking.

Numerous magnetic resonance imaging (MRI) studies have identified characteristics of carotid plaque related to cerebral vascular diseases [30], but there is no clinical research associated with TCM. Thus, we design this randomized, double-blind, parallel-controlled study and high resolution magnetic resonance imaging (HR-MRI) is used to correctly assess the efficacy of SMYA in the treatment of carotid atherosclerotic plaque. In the meantime, this study will also explore the internal mechanism of SMYA in the treatment of As, through transcriptome analysis, proteomic analysis, and metagenomic analysis of blood and stool. If successful, the finding will be valuable in the treatment of As plaque and drug development, and provide a reliable evidence chain.

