### Statistical analysis plan

This study will adopt an intention-to-treat analysis. And statistical analysis will be conducted by special statisticians in a blind way. SAS (6.12) will be used for statistical analysis, all statistical tests are conducted by two-sided tests, and *p* ≤ 0.05 is regarded as statistically significant. We will first analyze the baseline balance to explain whether the intervention group and control group of basic conditions are comparable. Quantitative metrics will be described with a number of cases, mean, standard deviation, median, minimum, and maximum, and t test or Wilcoxon rank sum test will be adopted to compare two groups. Qualitative metrics will be listed in frequency and percentages, and chi-square test or Fisher’s exact test will be conducted to compare two groups. For the analysis of combined medication, we will list the number and percentage, and analyze the differences between the two groups by the chi-square test or Fisher’s exact test. Analysis of treatment compliance will list the number and percentage of cases with experimental drugs < 80%, > 120%, 80-120%, and chi-square test or Fisher’s exact test will be conducted. In terms of safety analysis, we will describe the incidence of AEs and SAEs during the treatment period, and list the detailed tables of AEs and SAEs.

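### The 36 per group does not follow from the printed inputs, which give 26 to 28 if they share one unit; if the effect is a percentage and the SDs are micrometres, neither 36 nor 90% power can be verified

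*Protocol article*

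**What the plan says.** All the inputs stand in one paragraph, Sample size calculation:

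- Effect: "SMYA is expected to increase the plaque minimum fiber cap thickness (PMFCT) by an average of 40% µm".
- Spread: "The standard deviation of the experimental group in the intervention of carotid plaque FCT is about 38, and the control group is about 36". No unit is printed.
- Error rates and design: "This trial is designed as a 1:1 parallel control, α = 0.01, power = 90%, two-sided test".
- Result before drop-out: "According to the calculation, 36 participants are needed for each group".
- Allowance for drop-out, applied after that result: "After considering drop-out rates, the sample size of this protocol is 43 participants in the intervention group and the control group respectively". The total is 86.

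The Statistical analysis plan section sets a different significance threshold: "all statistical tests are conducted by two-sided tests, and *p* ≤ 0.05 is regarded as statistically significant".

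**The concern.** The paragraph prints its inputs and its answer, so it can be checked directly, and the two disagree. The effect also carries two incompatible units, so a reader cannot tell whether the target is an absolute gain of 40 µm or a relative gain of 40%.

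This paragraph is the only justification given for 86 participants and the only statement of the effect the trial is meant to detect on its primary outcome. If it stands as printed, the quoted 90% power describes no calculation a reader can repeat. A null result would also be hard to interpret, because the difference that the trial was built to find is not known.

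**Working it through.** **Inputs** (Sample size calculation): difference 40; SDs 38 and 36; two-sided alpha 0.01; power 90%; 1:1 allocation. Sum of variances: 38² + 36² = 1444 + 1296 = 2740. Pooled SD: √(2740/2) = 37.01.

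**1. Attempt to reproduce 36, with all values in one unit.** This covers all three in micrometres and all three in percentage points.

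n per group = (z for alpha/2 + z for power)² × (SD₁² + SD₂²) / difference²

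= (2.5758 + 1.2816)² × 2740 / 40² = 14.88 × 2740 / 1600 = 25.48, so **26**.

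The noncentral t calculation gives 27.19, so **28**. Neither is 36.

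**2. Variants that might explain 36.**

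| Variant (difference 40) | n per group: normal / t |
|---|---|
| SD 36 in both arms | 25 / 26 |
| SD 38 in both arms | 27 / 29 |
| Alpha 0.05 two-sided, pooled SD | 18 / 20 |
| Alpha 0.001 two-sided, pooled SD | 36 / 39 |

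Inflating the t figure of 28 for a Wilcoxon test gives 30 (relative efficiency 0.955) or 33 (0.864). Drop-out cannot fill the gap, because it is added after 36: for example 36/0.85 = 42.4, rounded up to 43. Only alpha 0.001 with the normal formula returns 36, and the article states 0.01.

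**3. What 36 and 43 per group deliver on the one-unit reading.**

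- 36 per group, alpha 0.01: standard error √(2740/36) = 8.72; 40/8.72 = 4.585; 4.585 − 2.576 = 2.009; power 97.8% (normal), **97.1%** (t).
- 43 per group, alpha 0.01: 99.3% (normal), **99.0%** (t).
- 36 per group, alpha 0.05: 4.585 − 1.960 = 2.625; power 99.6% (normal), **99.5%** (t).

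The difference for which 36 per group gives exactly 90% power at alpha 0.01 is √(14.88 × 2740/36) = 33.7 (normal) or 34.5 (t), not 40.

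**4. The mixed reading: effect 40%, SDs in micrometres.** The difference is then 0.40 × baseline mean, and no baseline is printed. The baselines below are assumptions, used only to show how far the answer moves (t test, alpha 0.01).

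| Assumed baseline (µm) | Difference (µm) | n per group for 90% | Power at 36 per group |
|---|---|---|---|
| 60 | 24 | 73 | 54% |
| 80 | 32 | 42 | 84% |
| 90 | 36 | 34 | 93% |
| 100 | 40 | 28 | 97% |
| 120 | 48 | 20 | over 99% |

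A baseline of about 34.5/0.40 = 86 µm would make 36 per group correct at 90%. The article neither supports nor excludes such a value.

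**The case against.** The strongest reply has three parts.

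- **The 26 to 28 depends on a unit that the article garbles.** This stands. On the mixed reading a baseline near 86 µm would make 36 right. The supportable statement is therefore conditional: 36 is wrong if the values share a unit, and cannot be verified if they do not.
- **On the one-unit reading the error is conservative.** This also stands. No participants need to be added, and the correction is to the text. It does not make the paragraph right, because the printed inputs and output still disagree by 8 to 10 per group.
- **An article condenses the full protocol.** That excuses an omitted drop-out rate, an omitted reference, or silence on whether the SDs are of the final value or of the change. It does not excuse printed figures that conflict or an unusable unit.

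Some stronger readings are tempting but not supported:

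- *The trial is underpowered.* On the one-unit reading it is not; on the mixed reading the power is unknown. The documents also give no basis for assuming SDs larger than those printed.
- *The planning values have no HR-MRI source.* The Introduction says of carotid plaque MRI studies "but there is no clinical research associated with TCM", and reports the team's own clinical study for hs-CRP. That makes an HR-MRI source within traditional Chinese medicine doubtful. It does not say where the SDs came from, and a missing citation makes a value unverifiable, not wrong.
- *A known slip produced 36.* At alpha 0.05 the normal formula gives 18 per group, 36 in total; at alpha 0.001 it gives 36 per group. Both fit the number, and the text cannot decide between them.

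**Conclusion.** The point holds in conditional form. With effect and SDs in one unit, the stated inputs require 26 (normal) or 28 (t) per group, not 36. The stated 90% power should then read about 97% for 36 evaluable per group at alpha 0.01, and 43 per group would give about 99%. With a percentage effect and micrometre SDs, neither 36 nor 90% can be verified without a baseline mean.

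The one-unit result takes the printed SDs at face value and assumes a two-sample comparison of means. The choice of alpha adds a further ambiguity: the size was set at 0.01, while the analysis declares significance at 0.05. On the one-unit reading, 36 per group give about 99.5% power at that threshold. This is an error in a figure the trial relies on, but correcting it does not call for a change in enrolment.

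**What to change.** Correct the Sample size calculation paragraph:

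1. State the effect and both SDs in one unit. If the effect is relative, add the baseline mean PMFCT it applies to.
2. Reconcile the design alpha of 0.01 with the threshold of 0.05 in the Statistical analysis plan section, and say which one governs the primary test.
3. Keep 86 participants, and restate the power that 36 evaluable per group deliver on the corrected inputs: about 97% at alpha 0.01 or about 99.5% at alpha 0.05 if all values share one unit. If the effect is relative, recompute with the stated baseline.

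Optionally, before unblinding, compare the pooled SD of PMFCT from the trial's own readings with the planning SDs and report the difference the trial can detect.

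The cost is a rewording and a short recalculation. No extra participants, visits or scans are needed.

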### Randomization, allocation and blinding

The stratified blocked randomization method will be used in this protocol. A random code list will be generated by SAS (6.12), and The intervention group and the control group will be randomly assigned to the enrolled participants in a ratio of 1:1. This study selects double-blind method, subjects, clinical researchers, drug managers, statisticians, and other staff members will be blinded. The trial is also designed as a two-stage blind. The blinding is conducted by irrelevant personnel, and the blind record is formed. In order to ensure the quality of the blind method, all medicaments, including placebo, are required to be packaged uniformly. According to the *Standard for the Use of Food Additives in the National Standard for Food Safety* [34], the placebo is made from 5% raw materials and 95% dextrin based on the type and volume of the raw materials. Adding an extremely low dose of the raw material makes this placebo similar in appearance, color, smell, and taste to the therapeutic drugs, but without any pharmacological effects [35, 36].

The blind bottom will be sealed and stored. If the blind bottom is opened, it is necessary to indicate the person who opened it, the date, the reason, etc., and at the same time record it in the case report form (CRF). In case of emergency, or when the patient needs to be rescued and necessary to know what medicines the patient is taking, The corresponding emergency letters must be opened and read in the presence of researchers and research leaders. Once the emergency letter is opened, the participant with this number will withdraw from the trial, at the same time, CRF will record all details. All emergency letters shall be taken back with the CRFs after the study for blind review.

### Intervention method

The intervention group takes SMYA, while the control group receives SMYA placebo (containing 95% dextrin and 5% SMYA). Both groups of drugs are taken orally, 1 bag/time, 2 times/day. The medication lasts for 14 days every 10 weeks, with a total of 50 weeks. The investigational drugs and placebo are granules, provided by Beijing Tcmages Pharmaceutical Co., Ltd (Beijing, China) according to the double-blind principle. The placebo is the same as treatment medicine in color, smell, taste, and packaging. Table 2 shows the schedule of enrollment, interventions, and assessments.

**Table 2 Tab3:** Schedule of enrollment, interventions and assessments

Stage procedure	Screening stage/Baseline	During treatment								After treatment
	-1 ~ 0days	2weeks	12weeks	14weeks	24weeks	26weeks	36weeks	38weeks	48weeks	50weeks
Visit	1	2	3	4	5	6	7	8	9	10
Patient screening	×									
Sign informed consent form	×									
Fill in demographic information	×									
Past medical history	×									
Medical comorbidities and current medication	×									
Physical examination	×	×	×	×	×	×	×	×	×	×
General examination	×	×	×	×	×	×	×	×	×	×
Carotid artery ultrasound	×									×
Carotid artery HR-MRI	×									×
Inflammatory cytokines tests	×	×	×	×	×	×	×	×	×	×
Blood fat and blood sugar	×	×	×	×	×	×	×	×	×	×
Weight	×	×	×	×	×	×	×	×	×	×
Blood pressure	×	×	×	×	×	×	×	×	×	×
Liver function tests and kidney function tests	×	×	×	×	×	×	×	×	×	×
Routine blood investigations	×	×	×	×	×	×	×	×	×	×
Blood transcriptome analysis	×	×	×	×	×	×	×	×	×	×
Blood proteomic analysis	×	×	×	×	×	×	×	×	×	×
Stool metagenomic analysis	×	×	×	×	×	×	×	×	×	×
Adverse events record	×	×	×	×	×	×	×	×	×	×
Combination therapy medication record		×	×	×	×	×	×	×	×	×
Distribution of the medication	×		×		×		×		×	
Summary of the remaining medication		×		×		×		×		×
Trial Summary										×

#### Guidelines for drug combination

During the trial, original lipid-lowering medicines are allowed to be used, but Western and Chinese medicines that may lower serum hs-CRP or other inflammatory factors are not allowed, for example, antibiotics, Canakinumab, and colchicine. If the participants have concomitant diseases, which they must continue to maintain these medicines or treatments, the diseases, treatment, dosage, usage and use time shall be recorded in the CRF, in order to analyze and report when summarizing. At each visit, the researcher detailed records of whether participants took medicine on time, and recovered the participants’ remaining medicines to judge treatment compliance. Patient compliance = Actual total medication/Total medication required by the protocol×100%.

#### Outcome evaluation

##### Primary outcome

PMFCT should be recorded at baseline (visit 1) and after treatment (visit 10), and evaluated at the study endpoint.

**Secondary outcome**

Plaque fiber cap volume, Volume percentage of fiber cap, LRNC volume, Volume percentage of LRNC, Internal bleeding volume of plaque, Internal bleeding volume percentage of plaque, Plaque calcification volume, Volume percentage of plaque calcification, Lumen stenosis rate, Average and maximum of vessel wall thickness, Vessel wall volume, Total vessel wall load (vessel wall volume/blood vessel total volume) will be measured at baseline (visit 1) and at the end of the treatment (visit 10), evaluated at the study endpoint.Carotid atherosclerosis score (CAS) [37] will be recorded at baseline (visit 1) and at the end of the treatment (visit 10), evaluated at the study endpoint.

i.Low risk: When MWT ≤ 2 mm, CAS = 1.ii.Medium and low risk: When MWT > 2 mm and LRNC ≤ 20%, CAS = 2.iii.Medium and high risk: When MWT > 2 mm and 20%< LRNC ≤ 40%, CAS = 3.iv.High risk: When MWT > 2 mm and 40%< LRNC, CAS = 4.
(3)hs-CRP, IL-1β, and IL-6 will be recorded at baseline (visit 1), during the treatment period (visit 2, 3, 4, 5, 6, 7, 8, 9 ) and at the end of the treatment (visit 10), evaluated at the study endpoint.(4)Blood lipid (TG, TC, HDL-C, LDL-C) and blood glucose will be recorded at baseline (visit 1), during the treatment period (visit 2, 3, 4, 5, 6, 7, 8, 9 ) and at the end of the treatment (visit 10), evaluated at the study endpoint.(5)Blood pressure and weight will be recorded at baseline (visit 1), during the treatment period (visit 2, 3, 4, 5, 6, 7, 8, 9 ), and at the end of the treatment (visit 10), evaluated at the study endpoint.

### Safety outcome

General physical examination, including temperature, respiration, heart rate, and routine blood tests, liver function tests (ALT, AST), kidney function tests (Bun, Cr) are recorded at baseline (visit 1), during the treatment period (visit 2, 3, 4, 5, 6, 7, 8, 9) and at the end of the treatment (visit 10). In the meantime, possible AEs will be observed at any time after administration and will be recorded at any time. Subjects who are abnormal after treatment but normal before treatment will be monitored periodically until they return to normal. All AEs will be followed up until the participants are properly resolved.

### Mechanism investigation

To clarify the mechanism of SMYA in treating patients with carotid atherosclerotic plaque, stool, and blood are collected at baseline (visit 1), during the treatment period (visit 2, 3, 4, 5, 6, 7, 8, 9 ), and at the end of the treatment (visit 10), followed by transcriptome analysis, proteomic analysis, and metagenomic analysis. The fecal collection process will be carried out following the “Standards for Collection, Preservation, and Transportation of Fecal Samples in TCM Clinical Trials” [38]. 

### Quality control

#### Quality control of HR-MRI

Use 3.0T HR-MRI to scan the target vascular segment. By injecting Injection Dimeglumine Gadopentetate intravenously (according to body weight, 0.2 ml/kg or 0.1mmol/kg per time, the maximum dosage is 0.4 ml/kg at a time per time, Beijing Beilu Pharmaceutical Co., LTD ) to enhance T1-weighted imaging, we will measure the PMFCT and other plaque components. All carotid HR-MRI examinations are carried out in DHABUCM. We will use the CA coil to assist imaging and help to fix the participants’ necks and maintain a unified posture. The inspections require the same equipment and the same doctor to operate and third-party blind ultrasound image analysis is performed. All research information, including research institutions, participants, and technicians, is digitally shielded in the image. The images will be sent to Plaque Vision (Beijing) Diagnostic Technology Co., LTD., and be analyzed by two experienced clinicians using “MRI-PlaqueView” independently.

#### Quality control of trial

Before the clinical trial, all researchers and relevant staff, such as clinical researchers and drug administrators will receive unified training which is associated with a trial-specific process. The clinical researchers should fill in all cases according to the requirements of CRF, and as the original record, it cannot be changed. Laboratory data and imaging data in trials will be recorded, in addition, the original report (or copy) should be pasted on CRF. The data that are significantly higher or beyond the clinically acceptable range should be verified, and the doctors participating in this trial should make necessary explanations. The clinical supervisors regularly monitor and visit, sample and check the original data, hold regular meetings on specific issues, and timely feedback information in the form of monitoring reports and project briefings to improve the monitoring quality.

Investigators will fill in the CRFs truthfully and inspectors will check data regularly. The original record shall be kept clear and visible when modifying, and the correction shall be signed and dated by the investigators. CRFs will be submitted to the clinical trial data administrators after being checked by the supervisors. The transmission among researchers, supervisors, and data administrators will have special records. Data administrators will check data again before entering data, and any questions and answers will be saved as question forms for future reference.

### Data management

In drug clinical trial institutions of DHABUCM, EpiData3.1 data management software is used, and establish a data bank. Inputers use double entries independently to input data. After data entry, spot-check some CRFs to define the entry quality and deal with existing problems. The data administrators check the data bank with the main researchers. The original CRFs shall be filed and saved after data entry and verification as required. Electronic data files containing data banks, inspection procedures, analysis results, codebooks, and description files, have several backups and will be saved on different record media properly. All original files should be saved according to “China’s Drug Clinical Trial Quality Management Standard” within the specified time.

### Statistical analysis plan

This study will adopt an intention-to-treat analysis. And statistical analysis will be conducted by special statisticians in a blind way. SAS (6.12) will be used for statistical analysis, all statistical tests are conducted by two-sided tests, and *p* ≤ 0.05 is regarded as statistically significant. We will first analyze the baseline balance to explain whether the intervention group and control group of basic conditions are comparable. Quantitative metrics will be described with a number of cases, mean, standard deviation, median, minimum, and maximum, and t test or Wilcoxon rank sum test will be adopted to compare two groups. Qualitative metrics will be listed in frequency and percentages, and chi-square test or Fisher’s exact test will be conducted to compare two groups. For the analysis of combined medication, we will list the number and percentage, and analyze the differences between the two groups by the chi-square test or Fisher’s exact test. Analysis of treatment compliance will list the number and percentage of cases with experimental drugs < 80%, > 120%, 80-120%, and chi-square test or Fisher’s exact test will be conducted. In terms of safety analysis, we will describe the incidence of AEs and SAEs during the treatment period, and list the detailed tables of AEs and SAEs.

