**Methods/design:**

The assessment of SMYA clinical trial is designed as a randomized, double-blind, placebo-controlled study. The sample size is 86 cases in total, with 43 participants in the intervention group and the control group respectively. The intervention group takes SMYA, while the control group takes SMYA placebo. The medication lasts for 14 days every 10 weeks, with a total of 50 weeks. We will use carotid artery high resolution magnetic resonance imaging (HR-MRI) to measure plaque. The plaque minimum fiber cap thickness (PMFCT) is adopted as the primary outcome. The secondary outcomes include plaque fiber cap volume, volume percentage of fiber cap, lipid-rich necrotic core (LRNC) volume, volume percentage of LRNC, internal bleeding volume of plaque, internal bleeding volume percentage of plaque, plaque calcification volume, volume percentage of plaque calcification, lumen stenosis rate, average and a maximum of vessel wall thickness, vessel wall volume, total vessel wall load, carotid atherosclerosis score, hs-CRP, IL-1β and IL-6, the level of lipid profiles and blood glucose, blood pressure, and body weight.

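### The only stated test for the primary PMFCT outcome is an unadjusted two-group comparison: valid, but it gives up precision that the scheduled baseline scan would supply at no cost

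*Protocol article*

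**What the plan says.** The abstract names the outcome: "The plaque minimum fiber cap thickness (PMFCT) is adopted as the primary outcome". Under Primary outcome, its timing is given as: "PMFCT should be recorded at baseline (visit 1) and after treatment (visit 10), and evaluated at the study endpoint". The schedule in Table 2 likewise has HR-MRI at visits 1 and 10 only.

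Under Randomization, allocation and blinding: "The stratified blocked randomization method will be used in this protocol". The factors are not named.

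Under Statistical analysis plan, the method for every quantitative variable is: "t test or Wilcoxon rank sum test will be adopted to compare two groups". No covariate or stratum term appears there or elsewhere. The one stated use of baseline data is a balance check: "We will first analyze the baseline balance to explain whether the intervention group and control group of basic conditions are comparable". The section on subgroup analyses splits participants by lipid-lowering therapy, which does not adjust the primary comparison.

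The article does not say whether week-50 values or changes from baseline are compared.

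**The concern.** Cap thickness at baseline will usually predict cap thickness a year later, so part of the between-patient spread at week 50 can be removed by conditioning on baseline. A two-group test on week-50 values uses none of that information. A two-group test on changes uses it with a fixed coefficient of 1, which is generally not the best weight. A balance check leaves the estimate and its standard error as they were.

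Stratifying the randomisation and then analysing as if it were unstratified leaves the standard error somewhat too large whenever the factors predict the outcome. With 36 evaluable participants per arm, what is at stake is the width of the confidence interval for the main result, and power if the true effect is smaller than planned.

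**Working it through.** **Inputs from the article (Sample size calculation, Statistical analysis plan)**
- Planned effect: "SMYA is expected to increase the plaque minimum fiber cap thickness (PMFCT) by an average of 40% µm". The unit is not usable as printed. I read it as 40 µm, which is an assumption.
- SD 38 (experimental) and 36 (control), pooled √((38² + 36²)/2) = 37.01. The article does not say whether these are SDs of final values or of change.
- Planning level: "This trial is designed as a 1:1 parallel control, α = 0.01, power = 90%, two-sided test". Analysis level: "all statistical tests are conducted by two-sided tests, and *p* ≤ 0.05 is regarded as statistically significant". The two differ, so both are shown.
- 36 evaluable per arm, 43 randomised per arm.

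**Assumed:** baseline to week-50 correlation r of 0.3, 0.5 or 0.7, and equal variances at the two times.

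**The plan's own figure.** n per arm = 2 × 37.01² × (2.576 + 1.282)² / 40² = 25.5, so 26 by the normal formula and 28 by the exact t calculation. The stated 36 does not reproduce. It would correspond to a difference of about 33.7 µm or a common SD of about 44. That is a separate matter, but it means the planned effect is not a firm anchor.

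**Variance of the treatment effect, relative to week-50 values.** Final value: 1. Change: 2(1 − r). ANCOVA: 1 − r². ANCOVA relative to change: (1 + r)/2.

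| r | Change | ANCOVA | ANCOVA cut vs final value | ANCOVA cut vs change |
|---|---|---|---|---|
| 0.3 | 1.40 | 0.91 | 9% | 35% |
| 0.5 | 1.00 | 0.75 | 25% | 25% |
| 0.7 | 0.60 | 0.51 | 49% | 15% |

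**Confidence interval, 36 per arm, SD 37 taken as the final-value SD.** Standard error = 37 × √(2/36) = 8.72 µm. The 95% half-width is 1.994 × 8.72 = 17.4 µm unadjusted. Multiplying by √(1 − r²) = 0.954, 0.866 and 0.714 gives 16.6, 15.1 and 12.4 µm.

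**Power, 36 per arm, SD 37 as the final-value SD, noncentral t**

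| Difference | α | Week-50 t test | ANCOVA, r = 0.3 / 0.5 / 0.7 |
|---|---|---|---|
| 40 µm | 0.01 | 97.1% | 98.3% / 99.5% / >99.9% |
| 40 µm | 0.05 | 99.5% | 99.7% / 99.9% / >99.9% |
| 25 µm (illustrative) | 0.01 | 59% | 64% / 74% / 91% |
| 25 µm (illustrative) | 0.05 | 81% | 84% / 90% / 98% |

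**If 38 and 36 are SDs of change and changes are tested**, the 25 µm, α = 0.05 case starts from the same 81%. ANCOVA with SD 37 × √((1 + r)/2) then gives 94%, 90% and 87%. The direction is the same, but the gain shrinks as r rises.

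**The case against.** The strongest reply is that nothing here is wrong. A two-group test is unbiased under randomisation, chance baseline imbalance is already covered by its standard error, and ignoring strata makes it conservative if anything. On the plan's own inputs, with the effect read as 40 µm, power is about 97% without adjustment. All of this stands, and it limits the point to precision.

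A second reply is that the quoted sentence is a general rule in a condensed article, and that a fuller protocol or analysis plan may specify the primary model. It is true that the sentence reaches PMFCT only because nothing else does. But the article states a method rather than staying silent, and if an unshown plan already uses ANCOVA, the published text needs aligning with it.

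Three stronger readings are tempting, and the article does not support them:
- **That the primary result would be biased or its error rate inflated.** It would not, for the reasons above.
- **That the trial has only about 59% power.** That figure needs a 25 µm effect found nowhere in the article, the SD read as a final-value SD, and α = 0.01 although the analysis section uses 0.05.
- **That ignoring the strata costs a known amount, or that the choice between t and Wilcoxon will be made after seeing results.** The factors are unnamed, so their prognostic value is unknown. The article does not say when the test is chosen, and it states that the analysis is blinded.

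**Conclusion.** The point holds as a precision improvement. The stated analysis is valid but leaves an already scheduled baseline measurement unused in the estimate, or used suboptimally if changes are compared. The variance reduction from ANCOVA is 9% to 49% against week-50 values, or 35% to 15% against changes, for r from 0.3 to 0.7. These figures rest on an assumed correlation and on equal variances at the two visits. The power and interval figures rest further on which quantity the SD describes.

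Under the planned effect read as 40 µm, the practical gain is a tighter interval, since power is already high. The gain in power becomes material only if the true effect is smaller, as in the 25 µm illustration. Any extra gain from adjusting for strata cannot be sized from the article.

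**What to change.** Before unblinding, state that the primary analysis is an ANCOVA of week-50 PMFCT on treatment and baseline PMFCT, reporting the adjusted mean difference with its confidence interval. Name the stratification factors and add them to the model. Keep the t or Wilcoxon test as a sensitivity analysis.

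Use the same model for the continuous HR-MRI secondary outcomes, each with its own baseline value. Do not use it for the carotid atherosclerosis score, which is an ordinal 1 to 4 grade.

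The cost is a change of wording plus naming the strata. Baseline scans are already scheduled, strata are fixed at randomisation, and neither new data nor a larger sample is needed. The article describes recruitment as ongoing and analysis as blinded, so on its account the change can still be prespecified.
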